### Statistical analysis

The normally distributed data will be expressed as mean ± standard deviation, and independent sample t-test will be used for groups differences. The non-normally distributed data will be expressed by a median, and the Mann–Whitney U test will be used for groups differences. The count data will be described as frequency and percentage and Fisher's exact test will be used for groups differences. The survival curve will be analyzed with the use of Kaplan–Meier, and the log-rank test will be used to evaluate groups differences. The Cox proportional hazards model will be used to evaluate the hazard ratio. *P* < 0.05 is set as the significance level.

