### Secondary outcomes

The secondary outcome has four parts: pathology data, efficacy index, safety index, and follow-up data. The pathology data comprises the 4sb lymph node metastatic rate, the number of 4sb LNs dissected, the number of 12a LNs dissected, and tumor pathological staging. The efficacy evaluation index comprises operation time, intraoperative blood loss, and postoperative recovery status (time to get out of bed, time to pass gas, time to liquid food intake, time to semi-liquid food intake, and postoperative hospital stay). The safety evaluation index comprises complications and mortality ≤30 days after surgery. Intraoperative complications include injuries of the hepatic artery, common bile duct, portal vein, spleen and pancreas. Postoperative complications include biliary fistula, delayed hepatic artery and portal vein hemorrhage, pancreatic fistula, and other pancreatic injury-related complications. Follow-up data comprises 3-year or 5-year disease-free survival and OS.

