### Sample size

The sample size was calculated using PASS 11.0 software. The 12a lymph node metastatic rate was used as the main result in the sample size calculation. This study assumes that the 12a lymph node metastatic rate in the experimental group is not inferior to the control group. According to published literature (9), the 12a lymph node metastatic rate of the control group is estimated at 9.1%. Combined with clinical practice, the non-inferiority threshold is set to −7.4%. The size of the two groups of patients was determined with a 1:1 design, setting a significance level of *α* = 0.025 (unilateral), power at 80%, and loss to follow-up at 10%. We expect 524 patients to be registered, with 262 patients in each group.

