## Discussion

LNM is an important factor affecting the 5-year OS rate of gastric cancer patients. Therefore, the prognostic value of D2 lymphadenectomy in gastric cancer needs to be further improved (10). Saito (11) found that in 239 cases of lower-third gastric cancer undergoing D2 lymphadenectomy, the lymph node metastatic rate in the 4sb group was 2.2%, which was related to LNs invasion and advanced gastric cancer. Shu (12) found that the metastasis rate of 12a LNs was 2.67% (11/413), which was related to tumor location, depth of tumor invasion and LNs stage. For patients with advanced gastric cancer (stages III/IV) located in the lower third of the stomach, the metastasis rate of 12a LNs increased to 10.7% (11/103). The recurrence-free survival rate and OS rate of patients with 12a LNM were significantly worse. Other studies have shown that the metastasis rate of 12a LNs is 1.7%–20% and it may be one of the most important factors affecting prognosis (7, 9, 10, 13–15). Therefore, accurate lymphadenectomy plays a positive role in the prognosis. However, the scope of 4sb and 12a LND in D2 lymphadenectomy is not clear. Lin (16) found that the unqualified rate of lymphadenectomy in 948 cases of laparoscopic total gastrectomy was 51.9%, and it gradually decreased with accumulated surgical experience. It is believed that the main reason for the unqualified LNs failure is the failure to dissect LNs at specific locations during the operation. Among them, the failure rate of the 12a LNs was higher (33.44%), and the No.4 LNs were lower (9.39%). This shows that a standardized and clear range of lymphadenectomy is significantly helpful for clinicians treating gastric cancer and undertaking complete D2 lymphadenectomy. However, there are few studies on the cleaning range of 4sb and 12a.

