Huang (17) pointed out that the posterior boundary of 12a LND was defined as the anterior edge of the portal vein, so only the LNs in front of the portal vein were cleaned during the operation. Huang (14) published a new 12a LND sequence, suggesting that the portal vein should be exposed first and the LNs before the portal vein should be cleaned. However, we considered that the 12a lymph node metastatic rate is lower for advanced lower third gastric cancer, and LNM around the portal vein is even more rare. Therefore, we suggested that only the LNs area in the front of the PHA should be cleaned, retaining the LNs area around the portal vein. The same is true for the 4sb LNs. We suggested cleaning the LNs around the first branch of the LGA and retaining the LNs around the root of the LGA. Through such a cleaning method, under the premise of ensuring the radical cure of the tumor, the risk of damage to blood vessels and organs, and complications during surgery, are reduced.

Although ESMO, NCCN and JGCA regularly update the guidelines for treating gastric cancer, they are all updated in terms of indications of the extent of LND, and there is no further detailed update of the definition of LND (4–6). In addition, although there have been some studies on 4sb and 12a LNs, the majority are related to LNM and risk factors or survival rates. Therefore, we are currently conducting a clinical trial to establish a safer 4sb and 12a LND range, to reduce the complication rate of D2 lymphadenectomy while obtaining the same radical cure effect.

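### The 4sb metastatic rate is tested only for a difference, with no margin, so a non-significant result cannot show that the limited 4sb dissection is adequate; the non-inferiority conclusion reaches 12a only

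*Protocol article*

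**What the plan says.** Under Experimental group and Control group, the new operation removes less tissue at both stations: it leaves the 4sb nodes at the root of the left gastroepiploic artery and the 12a nodes behind the proper hepatic artery. The Discussion gives the purpose as "to establish a safer 4sb and 12a LND range", with cure maintained.

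The Sample size section is confined to one station: "The 12a lymph node metastatic rate was used as the main result in the sample size calculation". It states a non-inferiority hypothesis for 12a, a 9.1% control rate and a threshold of 7.4 points, and concludes: "We expect 524 patients to be registered, with 262 patients in each group". No margin or precision target is given for 4sb.

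Under Secondary outcomes, "The pathology data comprises the 4sb lymph node metastatic rate", together with the number of 4sb nodes removed. Statistical analysis then fixes the method: "The count data will be described as frequency and percentage and Fisher's exact test will be used for groups differences", with the rule that P "< 0.05 is set as the significance level". Sidedness is not stated.

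The only 4sb rate in the article is in the Discussion, for 239 lower-third cases after D2 dissection: "the lymph node metastatic rate in the 4sb group was 2.2" per cent, "which was related to LNs invasion and advanced gastric cancer".

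**The concern.** If the limited scope is to be called equally curative at 4sb, the data must exclude an important loss of 4sb metastases. A test of difference does not do that. When it is non-significant, it leaves open every loss that the trial was too small to detect, and with a rare event that range is wide.

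A non-inferior 12a result does not fill the gap, because it concerns another station. If the two results are reported together, a reader could take a non-significant 4sb comparison as support for sparing the root nodes when the comparison could hardly have come out otherwise.

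**Working it through.** **Inputs.** 262 per group (Sample size). Fisher's exact test at P < 0.05 (Statistical analysis), taken as two-sided. Control 4sb rate 2.2% (Discussion); 3%, 4% and 5% are my assumptions, to show sensitivity.

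**The plan's own figure.** For 12a, with equal rates of 9.1%, margin 7.4 points, one-sided 0.025 and 80% power:

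n = (1.960 + 0.842)² × 2 × 0.091 × 0.909 / 0.074² = 237.1, so 238 per group. 238 × 1.10 = 261.8, so 262 per group and 524 in total. The stated size is reproduced, and it is a 12a calculation throughout.

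**What Fisher needs at 4sb.** With 0 positives of 262 in the experimental group and x of 262 in the control group, the one-sided P is C(262, x)/C(524, x), and the two-sided P is twice that:

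- x = 5: P = 0.061
- x = 6: P = 0.030

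So at least 6 control positives are needed. At 2.2% the expected number is 262 × 0.022 = 5.8.

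**Complete loss (2.2% vs 0%).** The test misses it when the control count X is 5 or fewer, with X ~ Binomial(262, 0.022): P(X ≤ 5) = 0.483.

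**Loss of half (2.2% vs 1.1%).** Summing the two binomials over all tables with Fisher P < 0.05 gives power 0.084, a miss rate of 92%.

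| Control 4sb rate | Complete loss missed | Loss of half missed |
|---|---|---|
| 2.2% (article) | 48% | 92% |
| 3% (assumed) | 20% | 87% |
| 4% (assumed) | 5% | 81% |
| 5% (assumed) | 1% | 75% |

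**Variants at 2.2%, complete loss.** If P < 0.05 is read as one-sided, 5 positives suffice and the miss rate is 32%. With 236 per group, after the planned 10% loss, the two-sided figure is 58%.

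**What an interval would show.** Take 5/262 (1.91%) in each group. Fisher gives P = 1. The Wilson limits for each group are 0.82% and 4.39%, so the Newcombe half-width is √[(4.39 − 1.91)² + (1.91 − 0.82)²] = 2.7 points. The interval runs from −2.7 to +2.7. It includes a loss of 1.91 points, the whole control rate, so identical results would not exclude complete loss.

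**The case against.** **Other outcomes bear on 4sb.** A reader might infer that 4sb is judged by Fisher's test alone. The article does not support that: it also compares the number of 4sb nodes removed, disease-free survival and overall survival. Neither closes the gap, though. The node count should fall by design, and survival cannot separate 4sb from 12a because both change together. The metastatic rate is the only outcome that directly measures 4sb capture.

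**The article never says that P > 0.05 will be read as adequacy.** This is correct. It describes its aim as exploratory, and its Conclusion admits lower-quality evidence and possible selection bias. Low power on a secondary outcome is ordinary, and interpretive detail may sit in documents not shown. What stands is that the article itself fixes a difference test for this outcome while aiming at a 4sb range with cure maintained.

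**2.2% is a literature rate, not a planning assumption.** This also stands. The cited series related 4sb metastasis to advanced disease, and this trial enrols cT2-4 and counts micrometastases as positive, so the rate may be higher. It would then be wrong to say that the test cannot tell nothing lost from everything lost: at 4% it misses complete loss in only 5% of trials. Partial loss remains poorly detected throughout, and it is the more realistic case because the limited scope still removes the first-branch nodes.

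**The 10% loss hardly applies.** The outcome is read from the operative specimen, so 262 per group is the fairer base, and 58% should not be the headline.

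**Transfers disturb the comparison.** Under Study design, experimental patients found node-positive before or during surgery join the control group. That moves positives from one group to the other, so two binomials with fixed rates are only an approximation. An interval computed on the groups after transfer would count the shift as apparent loss, and the fix has to deal with this.

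**There may be direct evidence.** Under Control group, nodes from two areas are examined separately. If those areas are first branch and root, the traditional dissection measures root-node metastasis itself. The wording is ambiguous, because the Experimental group section uses the same sentence, where the areas may be 4sb and 12a.

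**Conclusion.** The concern holds in a limited form. The 4sb metastatic rate has a difference test and no margin, and the non-inferiority design does not extend to it. A non-significant 4sb result therefore cannot establish that the limited scope is adequate.

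At 262 per group and a 2.2% control rate, complete loss would be missed in about 48% of trials and loss of half in about 92%. Across assumed rates of 3% to 5%, the miss rate falls from 20% to 1% for complete loss, and only from 87% to 75% for loss of half. These figures assume a two-sided test, independent binomial counts, equal groups and no transfers.

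The documents do not show that the trial will misreport 4sb, nor that no other evidence on 4sb will exist. The point is what this one comparison can support.

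**What to change.** 1. State that the non-inferiority conclusion applies to 12a only, and that P > 0.05 on the 4sb rate is not evidence of adequacy.
2. For the 4sb metastatic rate, replace the Fisher P value with the experimental-minus-control difference and its two-sided 95% confidence interval (Newcombe or Miettinen-Nurminen).
3. Analyse by the group assigned before any transfer, so that node-positive patients who were moved do not appear as loss. Say that this compares the two strategies, including the transfer rule, and that the interval does not allow for non-random assignment.
4. Word the between-group 4sb conclusion by the largest loss that the interval excludes. If the interval includes a loss equal to the control rate, report that this comparison does not rule out complete loss.
5. Clarify which two areas are examined separately. If they are first branch and root, also report the root-node metastatic rate in patients given the traditional dissection, with an exact 95% interval. For example, 0/262 has an upper limit of 1 − 0.025^(1/262) = 1.4%.

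The cost is analysis and wording, plus keeping a record of the assigned group. No patients are added and no procedure changes. The downside is that the trial gives up any 4sb claim resting only on a non-significant test.

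### Fisher's exact test for complications and 30-day mortality is valid but conservative for rare events; Boschloo's exact test keeps the 5% guarantee and adds about 2-4 points of power (minor, optional)

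*Protocol article*

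**What the plan says.** The Statistical analysis section of the protocol article names a single test for all categorical data: "The count data will be described as frequency and percentage and Fisher's exact test will be used for groups differences". The threshold follows at the end of the section: "0.05 is set as the significance level". Whether it is one- or two-sided is not stated; two-sided is taken here.

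Under Secondary outcomes, "The safety evaluation index comprises complications and mortality ≤30 days after surgery". These are binary per patient, so the Fisher rule applies to them, as it does to the 4sb metastatic rate.

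The only power statement is under Sample size. It concerns the 12a metastatic rate and ends with "We expect 524 patients to be registered, with 262 patients in each group". No complication rate, target difference or power is given for safety. Under Interim analyses, the primary and secondary outcomes are analysed once 262 patients are enrolled, and a significant disadvantage of the experimental group in effectiveness and safety leads to suspension.

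**The concern.** Fisher's test conditions on the total number of events. This design does not fix that total, so nothing requires the conditioning. With few events the conditional distribution is coarse, and the largest attainable rejection probability not exceeding 5% can be far below it. The test then gives up power that another exact test with the same guarantee can use.

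For a safety outcome this is not automatically the cautious side, because a true excess of complications is missed as readily as a true reduction. Fewer complications is a declared aim of the new dissection (Abstract, Introduction and Discussion). The listed events are specific vessel and organ injuries, fistulas and delayed bleeding, for which low rates are plausible. The sample size was set for another outcome, so the power for safety is whatever the chosen test leaves.

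**Working it through.** **1. The plan's own figure.** Inputs from Sample size: "the 12a lymph node metastatic rate of the control group is estimated at 9.1" per cent; "the non-inferiority threshold is set to −7.4" per cent; one-sided 0.025; "power at 80%, and loss to follow-up at 10" per cent. With equal true rates,

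n = (1.960 + 0.842)² × 2 × 0.091 × 0.909 / 0.074² = 7.849 × 0.16544 / 0.005476 = 237.1, so 238 per group.

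238 × 1.1 = 261.8, so 262. The stated group size is reproduced. It says nothing about safety.

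**2. Method for the safety comparison.** Let x and y be the numbers of patients with an event in two groups of n, and m = x + y. The two-sided Fisher P value P_F(x, y) is the sum of h(a) over all a with h(a) ≤ h(x), where h(a) = C(n,a) C(n,m−a) / C(2n,m). The rejection probability at true rates p₁ and p₂ is

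Σₓ Σᵧ Bin(x; n, p₁) Bin(y; n, p₂) · 1[P_F(x, y) ≤ c],

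summed over all (n+1)² tables (263 × 263 at n = 262). Setting p₁ = p₂ gives the size. Fisher's test uses c = 0.05. Boschloo's test uses the largest c for which the size, maximised over all common rates, stays at or below 5%. That c is about 0.059 at n = 262 and about 0.062 at n = 131. Since c exceeds 0.05, Boschloo's test rejects whenever Fisher's does and can never have less power.

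**3. True size of Fisher's test, nominal two-sided 5%, 262 per group.** Event rates are assumptions.

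| Common event rate | 0.5% | 1% | 2% | 3% | 5% | 10% |
|---|---|---|---|---|---|---|
| Size | 0.1% | 0.9% | 2.1% | 2.7% | 3.2% | 3.6% |

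The maximum over all common rates is about 4.2%.

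**4. Power at the final analysis, 262 per group.**

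| True rates | Fisher | Boschloo | Gain (points) |
|---|---|---|---|
| 1% v 4% | 50.2% | 53.3% | 3.1 |
| 2% v 5% | 38.2% | 42.1% | 3.9 |
| 3% v 8% | 66.5% | 69.2% | 2.7 |
| 5% v 10% | 53.5% | 55.6% | 2.1 |
| 10% v 18% | 71.6% | 74.6% | 3.0 |

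With 238 per group the gains are similar: 2.5 points at 1% v 4%, 3.8 at 2% v 5% and 2.4 at 5% v 10%. For very rare events the gain disappears: at 0.5% v 2% with 238 per group, power is 14.8% with either test.

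**5. Power at the interim look.** The 262 patients are the total, so about 262 / 2 = 131 per group if the groups are balanced then.

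| True rates | Fisher | Boschloo | Gain (points) |
|---|---|---|---|
| 1% v 4% | 17.9% | 23.8% | 5.9 |
| 2% v 6% | 25.3% | 30.8% | 5.5 |
| 3% v 8% | 31.5% | 37.0% | 5.5 |
| 5% v 10% | 25.0% | 28.8% | 3.8 |

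**6. The mid-P alternative.** Halving the probability of all tables tied with the observed one gives, at 262 per group, 59.6% at 1% v 4%, 46.2% at 2% v 5% and 57.9% at 5% v 10%, which is 9.4, 8.0 and 4.4 points above Fisher. Its maximum size is 5.05% at 262 per group and about 5.5% at 131, so the strict guarantee is lost.

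**The case against.** The strongest reply is that nothing here is wrong. Fisher's test is valid and standard for sparse tables, a significance level is a ceiling, and the ceiling is respected at every event rate. The article claims no power for safety, so no stated figure fails. All of this stands, and it is why the point is minor.

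A reader might infer that the plan discards 4-9 points of power for nothing. The documents do not support that. The larger gain belongs to mid-P, and it is bought by giving up the guarantee that Fisher provides. It also depends on how the two-sided mid-P is defined: halving only the observed table's probability gives smaller gains, about 2-6 points over the five pairs in step 4. Like for like, with the guarantee kept, the gain is the 2-4 points shown for Boschloo's test. Nor does a single range such as 1-3% describe the true size, since it depends on a rate the article does not give and runs from 0.1% to 3.6% over the rates in step 3.

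It can also be said that power for safety is modest with any of these tests, and that the test is not the main limit. The surgeon assigns the groups, experimental patients found node-positive move to the control group, and the Conclusion concedes possible selection bias. That is correct. Two independent binomial samples of equal size are an idealisation here, and no choice of unadjusted test removes confounding. It is a separate problem, however, and gives no reason to prefer a needlessly conservative test.

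**Conclusion.** The point holds as a minor, optional improvement. Fisher's test is a valid choice, but for rare safety events it works well below its nominal 5%, and an exact test with the same guarantee is never less powerful. The benefit is about 2-4 points at the final analysis and about 4-6 at the interim look for the pairs tabulated, and practically nil for the rarest events.

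The sizes rest on assumed event rates, two-sided testing, independent groups of equal size, and 131 per group at the interim. The direction does not depend on the assumed rates: Boschloo's test cannot do worse than Fisher's. The change would not make the safety comparison well powered, and it would not make it unconfounded.

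**What to change.** In the Statistical analysis section, for complications, 30-day mortality and the other binary secondary outcomes, replace Fisher's exact test by Boschloo's exact unconditional test, two-sided at 5%, and report the risk difference with a 95% score-type confidence interval beside it. The interval is at least as useful as the test, because it shows which excess or reduction in complications the data leave open. Outcomes with more than two categories, such as pathological stage, are not affected.

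The cost is one sentence, with no change to patients, data or procedures; the sentence should be fixed before outcomes are compared by group. Mid-P is not the recommended replacement, because it gives up the strict level guarantee.

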### Primary outcome

The primary outcome is the 12a lymph node metastatic rate. The 12a lymph node metastatic rate is equal to the number of patients with 12a LNM divided by the total number of patients enrolled.

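### The trial is sized for non-inferiority with a −7.4-point margin, but the only stated test for the primary outcome is Fisher's exact test of equality

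*Protocol article*

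**What the plan says.** In the protocol article, the Primary outcome section states: "The primary outcome is the 12a lymph node metastatic rate". It defines this as the "number of patients with 12a LNM divided by the total number of patients enrolled", a binary result per patient summarised as a proportion.

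The Sample size section sets the hypothesis: "This study assumes that the 12a lymph node metastatic rate in the experimental group is not inferior to the control group". It adds that "the 12a lymph node metastatic rate of the control group is estimated at 9.1" per cent and that "the non-inferiority threshold is set to −7.4" per cent, with one-sided alpha 0.025, 80% power, 1:1 groups and 10% loss, giving 262 per group and 524 in total.

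The Statistical analysis section is organised by type of data. For count data it gives frequencies, percentages and Fisher's "exact test will be used for groups differences". It sets one significance level, P < 0.05. It mentions no margin, no confidence interval for a rate difference and no one-sided level. No other section gives a separate analysis of the primary outcome.

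**The concern.** The design and the analysis ask different questions. The design asks whether the experimental rate is less than 7.4 points below the control rate. Fisher's test asks whether the two rates are equal. Not rejecting equality is not evidence that a deficit of 7.4 points has been excluded, and rejecting equality does not show a deficit beyond the margin.

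Followed as written, the final analysis never tests the hypothesis for which 524 patients are recruited. The Introduction and Discussion state the aim of easing the operation without loss of radicality. A non-significant Fisher result would then be the only primary finding available to support that aim. Such a result also becomes easier to obtain as the trial gets smaller or noisier, which is the reverse of what a non-inferiority design should reward.

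**Working it through.** **Inputs.** Control rate 9.1%, margin 7.4 points, one-sided alpha 0.025, power 80% and loss 10% come from the Sample size section. The experimental rate used for planning is not stated; I assume it equals the control rate. A lower experimental rate is taken as worse (positive nodes not found), as the negative sign of the margin implies.

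**1. Reproduce the stated size.** With the unpooled normal approximation:

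n = 2 × p(1 − p) × (z₀.₉₇₅ + z₀.₈₀)² / margin²
= 2 × 0.091 × 0.909 × (1.960 + 0.842)² / 0.074² = 237.1, rounded up to 238 per group.

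238 × 1.10 = 261.8, rounded up to 262 per group and 524 in total, exactly as stated. Tests of a difference do not give this figure. At two-sided 0.05 and 80% power, before dropout, 9.1% versus 1.7% needs 146 per group and 9.1% versus 16.5% needs 319. The 524 is therefore a non-inferiority sample size.

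**2. Compare the two decision rules.** Evaluable patients: 262 × 0.90 = 235.8, taken as 236 per group. I enumerated all pairs of counts from two independent binomials, with the control rate at 9.1%. For each pair I recorded whether two-sided Fisher gives p ≥ 0.05, and whether the lower limit of the two-sided 95% interval for experimental minus control lies above −7.4 points.

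| True experimental rate | True difference (points) | Fisher non-significant | Lower limit above −7.4: Wald | Lower limit above −7.4: Newcombe |
|---|---|---|---|---|
| 9.1% | 0 | 96.5% | 79.6% | 78.3% |
| 4.55% (half) | −4.55 | 56% | 25% | 21% |
| 3.0% (one third) | −6.1 | 24% | 10% | 8% |
| 1.7% (at the margin) | −7.4 | 5.0% | 3.7% | 2.2% |

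The interval rule gives the planned 80% power when the rates are equal. Fisher non-significance is a different event in every row.

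**3. How often the rules conflict.** Fisher is non-significant while the margin is not excluded in 19% (Wald) to 20% (Newcombe) of trials with equal rates, and in 31% to 35% at 4.55%.

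**4. Dependence on size.** At the margin (1.7%) with only 60 per group, Fisher is non-significant in 75.8% of trials, against 5.0% with 236.

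**5. One data set.** Control 21/236 (8.9%), experimental 12/236 (5.1%), difference −9/236 = −3.8 points.
- Fisher: p = 0.148, no significant difference.
- Wald standard error: √(0.0890 × 0.9110/236 + 0.0508 × 0.9492/236) = 0.0234. The 95% interval is −3.8 ± 1.96 × 2.34, or −8.4 to +0.8 points. The Newcombe lower limit is −8.6.

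The lower limit is below −7.4, so non-inferiority is not shown, although Fisher reports no difference.

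**The case against.** The Statistical analysis section is a generic paragraph in a condensed article. It does not name the primary outcome, and the full protocol and analysis plan are not shown. P < 0.05 is not in itself a conflict, because two-sided 0.05 corresponds to one-sided 0.025. Nowhere does the article say that a non-significant Fisher result will be read as non-inferiority. Rates of 4.55% and 3.0% both lie inside the margin, so accepting non-inferiority there is not a false claim by the plan's own definition. The false-claim rate belongs at 1.7%, where it is 5.0% against 2.5%. Finally, a new test cannot repair other weaknesses of the primary comparison, such as the different dissection fields or the move of node-positive patients into the control group.

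Much of this stands as qualification. The 56% and 24% show how often the two rules can give different answers; they are not type I error rates. The misreading is a risk, not a stated plan. The choice of interval method is ordinary analysis-plan detail. What does not stand is the appeal to silence. The section names a test and its purpose for all count data, with no exception for the primary outcome, and that test does not address the hypothesis in the Sample size section. An analysis plan that followed it would be wrong, and one that departed from it would contradict the published protocol. The other weaknesses are separate: whatever margin is kept, the analysis has to use it.

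**Conclusion.** The concern holds and must be fixed. The stated analysis of the primary outcome contradicts the stated hypothesis, and neither outcome of Fisher's test answers the non-inferiority question. If non-significance were read as non-inferiority, the error at the margin would be 5.0% instead of 2.5% at the planned size, and it would rise steeply in a smaller trial. With truly equal rates, about one trial in five would show no significant difference without having excluded the margin.

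These figures assume 236 evaluable patients per group, a 9.1% control rate, independent binomial counts and two-sided Fisher at 0.05. The contradiction itself depends on none of them. The sample size is not in question here.

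**What to change.** In the Statistical analysis section, give the primary outcome its own paragraph:

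- The primary analysis is the difference in 12a metastatic rate, experimental minus control, with a two-sided 95% confidence interval by the Miettinen-Nurminen or Newcombe method.
- Non-inferiority is claimed only if the lower limit lies above the pre-stated margin, which corresponds to one-sided alpha 0.025.
- Fisher's exact test is used for the secondary count outcomes only.

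A score-type interval is preferable to Wald, which passes 3.7% of trials at the margin against a nominal 2.5% (Newcombe 2.2%). The cost is wording in one section. The 524 patients remain adequate on the plan's own assumptions, with 78–80% power under the interval rule when both rates are 9.1%.
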